**Table 12.1: Sample Size Parameters**

|                                                     |                     |
|-----------------------------------------------------|---------------------|
| Significance level ( $\alpha$ )                     | 0.05                |
| Assumed responder rate ( $\pi$ )                    | 0.15                |
| Target width of $1-\alpha$ confidence interval (CI) | 0.30                |
| Probability of achieving target CI width            | 0.95                |
| Subgroup prevalence                                 | 0.25                |
| Attrition (%)                                       | 30                  |
| Total N (both subgroups)                     | 200 Subjects |

## **12.2. General Statistical Methods**

### **12.2.1. Analysis Sets**

All clinical endpoints will be analyzed on both intent-to-treat and a per-protocol basis. Safety endpoints will be analyzed in the safety analysis set.

- **Intent-to-Treat (ITT)**

In the intent-to-treat analysis, all enrolled subjects who undergo a Vercise DBS implant procedure will be included in the analysis.

- **Per-Protocol**

In the per-protocol analysis, only subjects completing all scheduled protocol visits through 52 weeks with no major protocol deviations will be included in the analysis. A comprehensive list of major protocol deviations will be provided in the Statistical Analysis Plan.

- **Safety Analysis Set**

In the safety analysis, all subjects who sign the IRB/EC-approved written Informed Consent form will be included.

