#### Safety Parameters

Rates of occurrence of all serious adverse events (SAEs) and all adverse device effects (ADEs), including serious adverse device effects (SADEs) and unanticipated serious adverse device effects (USADEs) at 3 years post first lead placement

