## **10. Subject Accountability**

### **10.1. Point of Enrollment**

A patient will be considered enrolled in this study after he/she signs and dates the informed consent form (ICF). No study-related procedures or assessments can take place until the informed consent form is signed.

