| Unlikely Related    | The relationship with the use of the device seems not relevant and/or the event can be reasonably explained by another cause, but additional information may be obtained.                                                                                                                                                                                                                                                                                                                                                                                                                                                                                                                                                                                                                                                                                                                                                                                                                                                                                                                                                                                                                                                                                                                                                                                                                                                                                                                                |

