**Table 20.4-1: Investigator Reporting Requirements**

| Event Classification | Communication Method | Communication Timeline post market studies*

(MEDDEV 2.12/2 :
GUIDELINES ON A MEDICAL
DEVICE VIGILANCE SYSTEM) |
|----------------------|----------------------|----------------------------------------------------------------------------------------------------------------------------|
|----------------------|----------------------|----------------------------------------------------------------------------------------------------------------------------|

regulatory approval and are used for the same approved indications.

\*\*Includes events that are related to hardware, stimulation and procedure

The investigator must report Adverse Device Effects, Serious Adverse Events (regardless of relationship to device hardware, stimulation and/or procedure), Unanticipated Serious Adverse Device Effects, and Device Deficiencies for each subject from the time of Information Consent through the end of study participation. AEs and Device Deficiencies may be reported via phone, fax or email if the electronic data capture (EDC) system is unavailable. The paper AE Notification Form or Device Deficiency Notification Form should be used to report AEs and/or device deficiencies during this time.

The Investigator must assess the potential relationship of all adverse events to the study device and/or to study procedures.

- Adverse events must be assessed according to their relationship to one of the following categories:
  - **Device Hardware-Related AEs:** AEs that can reasonably (i.e. Unlikely, Possibly, Probably and Causally Related) be attributed to the mere physical presence of the device or to deficiency of the device (i.e., an allergic response to device materials).
  - **Stimulation-Related AEs:** AEs that can reasonably (i.e. Unlikely, Possibly, Probably and Causally Related) be attributed to the effects of stimulation. A relationship to stimulation may be determined by demonstrating a predictable response to the alternating between stimulation-on and stimulation-off settings. However, a relationship to stimulation may also be reported without demonstrating a predictable response to the alternating between the stimulation-on and stimulation-off settings if in the opinion of the Investigator the AE is potentially related to stimulation.

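### Device-related safety rates are computed over everyone who signs consent, which dilutes them by the never-implanted share, and the protocol contradicts itself on whether an event rated Unlikely is related

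*Protocol*

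**What the plan says.** Section 12.2.1 of the protocol defines three analysis sets and assigns all safety outcomes to one of them: "Safety endpoints will be analyzed in the safety analysis set". That set is defined by consent: "In the safety analysis, all subjects who sign the IRB/EC-approved written Informed Consent form will be included". The same section already defines an implanted population, under the intent-to-treat label: "In the intent-to-treat analysis, all enrolled subjects who undergo a Vercise DBS implant procedure will be included in the analysis".

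The endpoint is in Section 7, Safety Parameters. It asks how often serious events and device effects of every class occur, and its closing words fix the time point for all of them: "unanticipated serious adverse device effects (USADEs) at 3 years post first lead placement".

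Enrolment precedes screening and surgery. Section 10.1 says: "A patient will be considered enrolled in this study after he/she signs and dates the informed consent form (ICF"). Section 10.2 lists, among the reasons for withdrawal, failing the criteria before implant and not receiving the sponsor's system. Section 10.4 stops enrolment at 200 implants. No limit or forecast is given for the number who consent.

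On relatedness, Section 20.4 describes stimulation-related events as "AEs that can reasonably (i.e. Unlikely, Possibly, Probably and Causally Related) be attributed to the effects of stimulation", and uses the same list of grades for hardware-related and procedure-related events. Table 20.3-1 assigns the grade Unlikely where the relationship with the device appears irrelevant and/or "the event can be reasonably explained by another cause". Table 20.2-1 defines an adverse device effect (ADE) as an adverse event related to use of the device.

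**The concern.** There are two separate problems.

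**Denominator.** A rate of device effects should be taken over people who could have had one. A subject who consents and is never implanted carries no Vercise hardware, receives no Vercise stimulation, and has no starting point from which three years can be counted. Including such subjects lowers the rates of ADEs, serious ADEs (SADEs) and unanticipated serious ADEs (USADEs) by an amount that reflects how sites screen, not how the device performs. A SAP that follows Section 12.2.1 faithfully would carry this over.

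**Numerator.** The protocol gives two incompatible readings of the grade Unlikely. In Section 20.4 it belongs with the reasonably attributable grades; in Table 20.3-1 it describes an event that something else reasonably explains. The choice can move the ADE count. It can also affect what is captured, because Section 14.1 records non-serious events only when they are related to device, stimulation or procedure. Sites that read the two passages differently may record different events.

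Safety rates are a named output of this registry, so their population and their definition of related should be unambiguous.

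**Working it through.** **The plan's own figure.** The only computed number in the protocol is the total of 200 implanted subjects (Table 12.1), which concerns precision of the responder rate. It implies 200 × 0.25 × 0.70 = 35 evaluable secondary-dystonia subjects. At a true rate of 0.15, the probability that the Clopper-Pearson interval is no wider than 0.30 is 0.931, close to the stated 0.95. This has no bearing on the safety question. No safety rate, precision or sample size is stated, so there is no safety figure to reproduce.

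**Step 1: dilution by the consent denominator.**
- From the protocol: implanted subjects, 200 (Section 10.4).
- Assumed: true three-year ADE risk in implanted subjects, r = 20%; share of consented subjects never implanted, s = 5% to 20%.
- Number consented = 200 / (1 − s). Reported rate = r × (1 − s), taking device effects as absent in the never-implanted.

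| s (assumed) | Consented | Reported rate for a true 20% |
|---|---|---|
| 5% | 200 / 0.95 = 210.5 | 40 / 210.5 = 19.0% |
| 10% | 200 / 0.90 = 222.2 | 40 / 222.2 = 18.0% |
| 20% | 200 / 0.80 = 250 | 40 / 250 = 16.0% |

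The relative understatement equals s whatever r is: a true 10% becomes 9.5% to 8.0%, and a true 30% becomes 28.5% to 24.0%.

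**Step 2: the relatedness passages side by side.** Section 20.4 treats four of the five grades (Unlikely, Possibly, Probably, Causal) as reasonably attributable. Table 20.3-1 defines the first of these by another cause being a reasonable explanation. Both cannot describe the same event as related. Section 20.4 is also the only place where the protocol groups grades as related, and an ADE is by definition a related event, so the route from this list to the ADE rate is short. No sentence in Section 12 states it.

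**Step 3: size if the Section 20.4 cut is used in the analysis.** Let u be the share of counted ADE subjects whose only events are rated Unlikely. The protocol does not give u. The reported rate is r / (1 − u). For r = 20%: u = 10% gives 22.2%, u = 20% gives 25.0%, and u = 50% gives 40.0%. These values of u are purely illustrative.

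**Step 4: both together.** The combined factor is (1 − s) / (1 − u), which equals 1 when u = s. For a true 20%:
- s = 10%, u = 20%: 0.20 × 0.90 / 0.80 = 22.5%.
- s = 20%, u = 10%: 0.20 × 0.80 / 0.90 = 17.8%.

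The net direction therefore depends on two quantities that the protocol does not supply.

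**The case against.** **A consented safety set has a purpose.** Sections 14.1 and 20.4 collect serious adverse events (SAEs) from consent, and the rate of all SAEs does not depend on relatedness. For events before implant, the consented set matches the collection window. This stands, and the fix keeps that set for that use.

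**Never-implanted subjects are not wholly free of related events.** Section 20.4 includes events tied to a protocol-required procedure. Under Section 11.5.1, Pocket Adaptor subjects switch stimulation off for the baseline assessments, before the implant. A consented subject who is never implanted could thus have a procedure-related event. This also stands. The dilution argument holds strictly for hardware and Vercise stimulation effects and would be slightly weaker for procedure-related ones.

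**The share never implanted may be small.** Candidates are already eligible for stimulation (Section 9.1), there is one exclusion criterion, and consent, screening and baseline may fall on the same day (Section 11.4). The lower end of the assumed range may be the more realistic. That reduces the size of the problem but not the mismatch.

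**The Unlikely list sits in a reporting section.** Treating everything not excluded as related is a cautious reporting rule, and the recorded grades allow any cut to be tabulated. It is fair that use of this cut in the analysed rate is inferred rather than stated. Two points remain. Caution does not require it, because Table 20.3-1 already sends unassessable cases to Possibly. And later tabulation works only if sites have recorded non-serious Unlikely events uniformly, which the contradiction puts in doubt.

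**A stronger reading to avoid.** With 30% attrition in Table 12.1 and no data after withdrawal (Section 10.2), a reader might infer that early leavers will be counted as event-free. The protocol does not say so. Section 12.3 has only a general sentence about descriptive summaries and names no estimator for the safety rates. That choice is commonly left to the SAP, which is not at hand.

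**Conclusion.** The point holds in two parts of unequal firmness.

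The denominator part is firm. Section 12.2.1 and Section 7 do not fit together, and following them as written multiplies device-related rates by (1 − s). On the assumed 5% to 20% never implanted, a true 20% would be reported as 19.0% to 16.0%. The actual s is unknown.

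The contradiction over Unlikely is also firm as a matter of text. Its effect on the analysed ADE rate is conditional: if the Section 20.4 cut is carried into the analysis, the rate is inflated, by an amount that cannot be computed from the document.

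A reader might conclude that the safety figures as a whole will be wrong, or wrong in a known direction. The protocol does not support that. The two mechanisms oppose each other, their sizes are not given, and the all-SAE rate is untouched by the relatedness question.

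Severity is moderate: the registry is descriptive, states no safety hypothesis or threshold, and already defines the population needed to put the denominator right.

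**What to change.** 1. In Section 12.2.1, make subjects who undergo a Vercise implant procedure (the population now labelled intent-to-treat) the denominator for ADE, SADE and USADE rates and for post-implant SAE rates. Keep the consented set for SAEs collected from consent, and list any pre-implant procedure-related event there.
2. Reconcile Table 20.3-1 with Section 20.4 so that Unlikely has one meaning, and state plainly whether non-serious events with that grade are to be recorded, so that sites do so uniformly. Leave expedited reporting unchanged.
3. Report related-event rates twice: with and without events rated Unlikely.

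The cost is a few sentences of protocol wording, mirrored in the SAP (Section 12.3.5 already provides for amending it before analysis), plus one extra column in the safety tables. Relatedness grades and implant dates are already collected. The downside for the sponsor is that device-related rates over implanted subjects will look slightly less favourable than over consented subjects.

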### **12.2.2. Control of Systematic Error/Bias**

Selection of patients will be made from the Investigator's usual patient population, including referred patients. All patients meeting the inclusion/exclusion criteria and having signed the Informed Consent Form will be eligible for participation in the study. The reasons for exclusion, for patients who sign an informed consent form, but are not enrolled, will be indicated in the patient screening log. Consequently, consecutively eligible patients will be enrolled in the study, minimizing selection bias. BSC will report to the relevant competent authorities any evidence of fraud, including deliberate tampering with the selection of patients.

### **12.2.3. Number of Subjects per Investigative Site**

Enrollment will be competitive across sites, with an initial maximum of 10 implanted subjects at any one site. The per-site implant cap of 10 subjects may be increased upon Sponsor approval. At the time when the study-wide enrollment cap is reached, further enrollment into the study will cease regardless of whether individual sites have reached their per-site cap.

### **12.3. Data Analyses**

Post-procedure information will be collected at regularly scheduled follow-up examinations as detailed in the clinical trial schedule and will be summarized using descriptive statistics for continuous variables (e.g., mean, standard deviation, n, minimum, maximum) and frequency tables or proportions for discrete variables.

All statistical analyses will be done using the SAS System software, version 8.1 or later (Copyright © 2000 SAS Institute Inc., SAS Campus Drive, Cary, North Carolina 27513, USA. All rights reserved).

#### **12.3.1. Interim Analyses**

The two subgroups in the study (primary dystonia and secondary dystonia) will be tested separately and no pooling across subgroups will be performed. Consequently, analysis will proceed when sufficient power is reached separately for each subgroup.

#### **12.3.2. Subgroup Analyses**

Results will be summarized for the following subgroups of subjects. These subgroup analyses are not powered, and will be for exploratory purposes only. These analyses are subject to availability of data.

- Age at surgery
- Age of disease onset
- Duration of disease
- Dystonia Classification
- Genetic status
- STN versus GPi implanted subjects

#### **12.3.3. Justification of Pooling**

Analyses will be performed using data pooled across institutions. Multivariate analysis techniques, including contingency tables and logistic regression for binary outcomes and analysis of variance for continuous measures, will be used to assess differences among study institutions to justify pooling data across institutions.

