### 8.1. Scale and Duration

The study will be conducted at up to 40 international centers. Up to 200 subjects will be implanted. Follow-up of each subject will continue for three years after first lead placement. The study may require up to five calendar years to complete.

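### Section 12.3.3 asks site-difference tests to justify pooling across institutions, but with 20 to 40 sites and subgroups of about 35 and 105 subjects a null test cannot support that

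*Protocol*

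**What the plan says.** Section 12.3.3 of the protocol opens by stating that analyses use data pooled across institutions, with no condition attached. It then names contingency tables and logistic regression for binary outcomes, and analysis of variance for continuous ones, which "will be used to assess differences among study institutions to justify pooling data across institutions". It gives no test level, no rule for sites with few subjects and no consequence if differences are found.

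The scale of the study is set in section 8.1: "The study will be conducted at up to 40 international centers. Up to 200 subjects will be implanted". Section 12.2.3 describes competitive enrolment "with an initial maximum of 10 implanted subjects at any one site", a cap that the sponsor may raise. Section 12.1 has all clinical endpoints evaluated separately for primary and secondary dystonia. Section 12.3.1 says that the two subgroups "will be tested separately and no pooling across subgroups will be performed".

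**The concern.** Using a test of site differences to justify pooling means reading a non-significant result as evidence that sites are alike. That reading has force only if the test would probably have detected differences of a size that matters. Here the subjects are few relative to the number of sites, above all in the secondary subgroup, so a null result is likely whether or not sites differ.

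Site differences are plausible. Section 11.6 acknowledges that centres have developed their own implant and programming practices, and the main rating scales are clinician-rated wholly or in part. The main output is a Clopper-Pearson interval for the responder rate (section 12.1.1), which treats subjects as independent, and section 12.1.2 makes the width of that interval the design goal. If outcomes cluster by site, the interval is too narrow. A null site test followed by a statement that pooling was justified would hide this.

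**Working it through.** **Inputs from the protocol.** Table 12.1 gives "Total N (both subgroups) | 200 Subjects", "Subgroup prevalence | 0.25", "Assumed responder rate ( $\pi$ ) | 0.15" and attrition of 30%. Sites number at most 40 (section 8.1). The cap of 10 implies at least 200 / 10 = 20 sites unless it is raised.

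**Subjects available.** Secondary: 200 × 0.25 × 0.70 = 35 (50 without attrition). Primary: 200 × 0.75 × 0.70 = 105.

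**The plan's own figure.** With n = 35 and a true rate of 0.15, summing the exact binomial probabilities of outcomes whose Clopper-Pearson 95% interval is at most 0.30 wide gives 0.931, against the stated 0.95. That is close enough to confirm 35 as the evaluable number behind the total of 200.

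**Secondary subgroup: sparsity.** With equal-probability accrual over k sites, the expected number of sites with at least one subject is k × [1 − (1 − 1/k)^35], and with exactly one subject 35 × (1 − 1/k)^34. The single-outcome share comes from simulation at a 15% response rate.

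| Sites | Occupied | Exactly one subject | Occupied sites with only one outcome | ANOVA residual df |
|---|---|---|---|---|
| 40 | 23.5 | 14.8 | 89% | about 11 |
| 20 | 16.7 | 6.1 | 78% | about 18 |

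At 40 sites only about 2.6 sites have both a responder and a non-responder. A site with one outcome has no finite maximum-likelihood estimate for its own term, and a one-subject site always has one outcome. The logistic model with a term for every site therefore fails under any realistic accrual pattern. Without attrition (50 subjects over 40 sites) the single-outcome share is still 84%.

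**Secondary subgroup: power of what can be run.** Simulated, 5% level:

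| Test | Sites | ICC 0.05 | ICC 0.10 | ICC 0.20 |
|---|---|---|---|---|
| ANOVA | 40 | 6% | 9% | 13% |
| ANOVA | 20 | 8% | 11% | 21% |
| Exact responder table, rate 0.15 | 40 | 2% | 5% | 8% |
| Exact responder table, rate 0.15 | 20 | 6% | 9% | 17% |

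**Primary subgroup.** With m = 105/k subjects per site, ANOVA power is P(F(k − 1, 105 − k) > Fcrit / [1 + m × ICC/(1 − ICC)]).

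- 40 sites: m = 2.625 and Fcrit = 1.584 on (39, 65) df. At ICC 0.10 the divisor is 1 + 2.625 × 0.111 = 1.292, the threshold 1.226 and the power 23%. At ICC 0.05 and 0.20 the power is 12% and 55%.
- 20 sites: m = 5.25 and Fcrit = 1.710 on (19, 85) df. At ICC 0.10 the divisor is 1.583, the threshold 1.080 and the power 39%. At ICC 0.05 and 0.20 it is 18% and 77%.

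Simulation with random site sizes agrees: 12%, 25%, 57% at 40 sites and 18%, 38%, 76% at 20. The responder table at an assumed rate of 0.5 gives 12%, 30%, 63% and 19%, 39%, 76%.

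**What a missed ICC would cost.** A primary subject shares a site with 104/k others on average, so the design effect is about 1 + (104/k) × ICC. At ICC 0.10 this is 1.26 (40 sites) to 1.52 (20 sites). The square roots, 1.12 and 1.23, mean that the interval should be roughly 12% to 23% wider.

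**The case against.** The strongest reply is that nothing depends on these tests. Pooling is stated outright, no decision rule follows, and the responder rate is reported descriptively by subgroup whatever the tests show. A reader might infer that pooling depends on passing a test, or that the reported estimates would change. Section 12.3.3 supports neither. What remains is the stated purpose: the tests are there to justify the pooling, and they cannot.

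A reader might also infer that none of the named methods can be fitted in the secondary subgroup. That is too strong. Empty sites drop out, ANOVA runs on the residual degrees of freedom shown above, and an exact table test can be computed. Only the logistic model with a term for every site fails. The section does not say that site enters as a fixed effect, and grouping small sites may be left to the statistical analysis plan.

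The subgroup premise is also open to challenge. Section 12.3.3 does not say that the site check runs within subgroup; that is inferred from sections 12.1 and 12.3.1. If all 140 evaluable subjects were used, the same formula gives 16%, 35%, 77% (40 sites) and 25%, 53%, 89% (20 sites) at ICC 0.05, 0.10, 0.20. Power is then respectable for large heterogeneity, but still only 16% to 53% at ICC 0.05 to 0.10.

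Finally, 40 sites is a maximum and the full 30% attrition is pessimistic for the 26-week visit. Both are fair, which is why ranges are given. Neither turns a null test into evidence of homogeneity at small or moderate ICC.

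**Conclusion.** The point holds as one about the inference that section 12.3.3 states. Pooling is already decided, and the tests named to justify it are close to uninformative in the secondary subgroup (power about 2% to 21%). In the primary subgroup they inform only about large heterogeneity (55% to 77% at ICC 0.20, against 12% to 39% at 0.05 to 0.10). One named method, logistic regression with every site as a term, has no finite solution in the secondary subgroup.

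The ICC range, equal-probability accrual, the 5% level for the site tests and the primary responder rate of 0.5 are assumptions; the protocol gives none of them. The endpoint estimates themselves remain computable, so this is a worthwhile and inexpensive improvement rather than a threat to the study.

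**What to change.** Reword section 12.3.3 to say that data are pooled across institutions by design and that no significance test serves as the justification. Describe between-site variation with a random site intercept (mixed logistic model for response, linear mixed model for scores), and report the site variance or ICC with its confidence interval, so that the reader sees how much heterogeneity the data leave open.

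If that model is fitted across all subjects with dystonia type as a covariate, label it as describing site variance only, so that endpoint estimates stay separate by subgroup as section 12.3.1 requires.

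Add a site-cluster-robust interval for the responder rate as a sensitivity analysis, at least in the primary subgroup; in the secondary subgroup there may be too few subjects per site to support it.

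The cost is a paragraph of protocol and analysis-plan wording and one additional model, with no new data or subjects. The sensitivity interval may come out somewhat wider than the Clopper-Pearson one.
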